## 5. TREATMENT OF SUBJECTS

### 5.1 Investigational treatment

#### Treatment with frequent nocturnal hemodialysis

Patients in this group are included in the study at the start of frequent nocturnal hemodialysis. Frequent nocturnal hemodialysis is defined as hemodialysis sessions of at least 7 hours, performed during 4-7 nights/week. Most often it will be performed as nocturnal home hemodialysis, but patients who perform frequent nocturnal hemodialysis in a dialysis center can also be included. Much experience with this treatment has been obtained, and results are excellent, and complications or technical problems are comparable with conventional hemodialysis. Blood flow during hemodialysis is 150 ml/min, dialysate flow is 300 ml/min. Dialysis fluid is different from the fluid in conventional hemodialysis regarding the following constituents: potassium 3 mmol/l, calcium 1.75 mmol/l, bicarbonate 30 mmol/l, phosphate supplementation when necessary.

#### Treatment with renal transplantation

Patients in this group are included in the study at the moment of renal transplantation, with a living or cadaveric renal transplant. Immunosuppressive medication is given according to the conventional standard regimens, and is adjusted as required by clinical events.

#### Treatment with conventional hemodialysis

Conventional hemodialysis is defined as hemodialysis sessions of a maximum of 5 hours, mostly 3-4 hours, performed 3-4 times a week. Hemodialysis is applied according to guidelines of the Dutch Nephrology Federation (NFN).

#### Treatment with peritoneal dialysis

Peritoneal dialysis is defined as treatment with continuous ambulatory peritoneal dialysis (CAPD) or continuous cyclic peritoneal dialysis (CCPD). Peritoneal dialysis treatment is applied according to guidelines of the NFN.

### 5.2 Co-intervention

#### Supportive treatment in nocturnal hemodialysis, conventional hemodialysis and peritoneal dialysis

Medications and diet in dialysis patients are prescribed according to the guidelines of the NFN regarding blood pressure regulation, treatment of anemia and acidosis. Treatment times on hemodialysis will be adjusted when total Kt/V is < 3.6/week. Treatment regimen on peritoneal dialysis will also be adjusted to reach a Kt/V of 1.7/week or 45 L/week. Regarding calcium and phosphate targets, KDOQI/NFN guidelines are also followed, i.e.:

- target phosphate  $\leq 1.78$  mmol/l
- calcium phosphate product  $\leq 4.4$  mmol/l (with calcium corrected for albumin: correction factor 0.02 mmol/l calcium per 1 g/l decrease in serum albumin below 42 g/l)

- PTH 16-33 pmol/l

In order to improve patient compliance to drug therapy, daily-dose blister packaging will be encouraged in all patients.

#### Supportive treatment in renal transplant patients

The following medication is given according to common practice:

- daclizumab or basiliximab in case of a second transplant, or in patients with increased immunologic risk
- ranitidine or pantozole during treatment with prednisolone
- cotrimoxazole during the first 4 months post-transplant
- valganciclovir in case of donor CMV IgG + antibodies/ recipient – antibodies
- calcium carbonate as osteoporosis prophylaxis in patients using prednisolone, unless hypercalcemia is present
- amlodipine
- other supportive medication according to common practice when appropriate e.g. for treatment of hypertension, rejection, and other post-transplant complications.

In order to improve patient compliance to drug therapy, daily-dose blister packaging will be encouraged in all patients.

When necessary for medical reasons, the treatment regimen will of course be adjusted to the need of the individual patient.

### **5.3 Escape medication**

Not applicable.

## **6. INVESTIGATIONAL MEDICINAL PRODUCT**

Not applicable.

## **7. METHODS**

### **7.1 Study endpoints**

#### 7.1.1 Main study endpoint

The primary endpoint of the study is:

- change in coronary artery calcification score

#### 7.1.2 Secondary study endpoints

The secondary endpoints of the study are:

- change in pulse wave velocity
- change in coronary artery stenosis
- association between calcium, phosphate, PTH and change in coronary artery calcification score
- association between high-sensitivity-CRP, interleukin-6, interleukin-1, von Willebrand factor, myeloperoxidase, and change in coronary artery calcification score
- association between fetuin A, osteoprotegerin and matrix-Gla protein, and change in coronary artery calcification score
- cardiovascular events and mortality, assessed by the local investigator and the principal investigator separately

#### 7.1.3 Other study parameters

Other parameters that will be studied are:

- body weight
- blood pressure
- laboratory parameters: hemoglobin, cholesterol, HDL-cholesterol, LDL-cholesterol, triglycerides)
- calcification propensity in serum
- quality-of-life questionnaire
- medication (antihypertensive medication, medication concerning calcium-phosphate-homeostasis and immunosuppressive medication)

### **7.2 Randomization, blinding and treatment allocation**

Not applicable.

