## **SUMMARY**

### **Rationale:**

Cardiovascular disease is the leading cause of mortality in patients with end-stage renal disease (ESRD). The vascular abnormalities in ESRD are especially characterized by arterial wall calcifications, whereas intimal hyperplasia seen with "classic atherosclerosis" is less pronounced. These calcifications are strongly associated with increased mortality. The exact mechanism by which calcification develops is unknown, but there is a direct relationship with increased serum calcium and serum phosphorus. With long and frequent hemodialysis, such as nocturnal hemodialysis, and with renal transplantation, calcium and phosphate levels can be normalized. It is unknown whether these treatments inhibit the progression of arterial calcification or bring about regression of calcification. The hypothesis of this study is that with nocturnal hemodialysis the progression of arterial calcification is less than with conventional hemo- or peritoneal dialysis, and approximates the progression rate seen with a renal transplant.

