**Nature and extent of the burden and risks associated with participation, benefit and group relatedness:**

- The study is an observational study, not an intervention-study.
- Participation does not influence or change the nature of the treatment, i.e. the modality of renal replacement therapy;
- Participation is associated with limited physical examination, questionnaires and blood sampling;
- Blood sampling is performed in combination with regular blood sampling, and requires a maximum of 20 cc blood per visit extra, once a year;
- Multislice CT-scan is performed at inclusion, and after 1, 2 and 3 years; this scan takes < 1 minute of time and radiation exposure is less than with conventional abdominal CT-scan; at inclusion and after 3 years, multislice CT-scan with intravenous contrast is performed to examine potential coronary stenosis.
- Yearly measurements of pulse-wave velocity are done with ultrasound (non-invasive), which takes 30 minutes of time.

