## **4. STUDY POPULATION**

### **4.1 Population**

The study populations consists of 4 cohorts of patients: patients who start with frequent nocturnal hemodialysis, patients who receive a renal transplant and 2 control groups treated with hemodialysis and with peritoneal dialysis. The study is sponsored by Dianet Dialysis Centers, while all research activities take place in University Medical Center Utrecht. Patients were screened at their local treatment facility (Dialysecentrum Groningen, Groningen; Dialysecentrum Diapriya, Amsterdam; VU medisch centrum, Amsterdam; Meander Medisch Centrum, Amersfoort; Rijnstate Ziekenhuis, Arnhem; Sint Antoniusziekenhuis, Nieuwegein; Stichting Dianet Dialysecentra, Utrecht and Amsterdam; and University Medical Center Utrecht, Utrecht), and if interested in the study, subsequently referred to University Medical Center Utrecht for study participation.

- 40 patients who start treatment with frequent nocturnal hemodialysis are asked to participate in the study;
  - 40 patients who receive a renal transplant, after having been treated with hemo- or peritoneal dialysis, are asked to participate in the study;
  - 40 patients who are treated with conventional hemodialysis are asked to participate; in order to enhance similarity between groups only hemodialysis patients are recruited that are or could be eligible to be on the waiting list for renal transplantation;
  - 40 patients who are treated with peritoneal dialysis are asked to participate; in order to enhance similarity between groups only peritoneal dialysis patients are recruited that are or could be eligible to be on the waiting list for renal transplantation.
- Groups will be matched according to age, sex, presence of diabetes mellitus and duration of dialysis, in order to minimize between-group differences to 25% regarding these factors.

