### **4.4 Sample size calculation**

The effects of the different modalities of renal replacement therapy on arterial calcification are analyzed with linear regression, after transformation of calcium scores. The effects of risk

factors for calcification, including inflammation parameters and calcification inhibitors are analyzed in a multivariate model. The mean ( $\pm$ SD) coronary calcification score in ESRD patients is 2370 ( $\pm$  352). The multislice CT-scan is extensively validated in our institute. At this level of calcification the variation between independent measurements is less than 10%. Therefore we can demonstrate an increase or decrease in calcification score of 15%, in 4 subpopulations of 22 patients with ESRD, with a type I error probability for a two sided test of 0.05 and a power of 0.90 [formula: " $N = (2(Z_{\alpha} + Z_{\beta})^2 \cdot sd) / (0.15 \cdot \text{mean})$ " where N = number of patients per group,  $Z_{\alpha} = 1.96$ ,  $Z_{\beta} = 1.28$ ,  $S = 3.52$ , mean = 2370]. To account for a dropout of patients by renal transplantation, switch to a different treatment modality, refusal of further participation or death we intend to include 40-55 patients per group – depending on the dropout, aiming to obtain complete study data in 22 patients per group.

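### Section 7.2 sets blinding aside without exception, so the CT scans behind the primary endpoint may be read with treatment group and time point known

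*Protocol*

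**What the plan says.** - **Blinding.** Protocol section 7.2 carries the heading "Randomization, blinding and treatment allocation". Its entire content is "Not applicable". No exception is made for image readers.
- **Primary endpoint.** Section 7.1.1 names "change in coronary artery calcification score". The Summary gives the schedule: "Multislice CT-scan is performed at inclusion, and after 1, 2 and 3 years".
- **Hypothesis.** The Summary (Rationale) expects that "with nocturnal hemodialysis the progression of arterial calcification is less than with conventional hemo- or peritoneal dialysis".
- **Where the work is done.** Section 4.1 says that "all research activities take place in University Medical Center Utrecht".
- **CT procedures.** Section 7.3 specifies scanner, acquisition, reconstruction, dose and contrast. It does not say who scores the scans, with what software, in what order, or with what knowledge of the patient.
- **Measurement variation.** Section 4.4 states, when describing validation of the scan: "At this level of calcification the variation between independent measurements is less than 10" per cent.
- **Assessors.** The only assessor rule is for a secondary endpoint in section 7.1.2: "cardiovascular events and mortality, assessed by the local investigator and the principal investigator separately". It concerns separate assessment, does not mention masking, and does not cover the CT reading.

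**The concern.** An observational design makes randomisation and allocation irrelevant, and it rules out masking of patients and treating staff. It does not rule out masking the person who scores an image. Section 7.2 treats all of these together, so unmasked reading of the primary endpoint is permitted.

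The endpoint is a difference between readings made at different times. A reader who knows the group, or which scan is baseline and which is follow-up, could score in line with the expected direction. If this differs between groups, it adds a shift to the group contrast. The shift is tied to group membership, so the covariate adjustment in sections 9.2 and 9.3 cannot separate it from a treatment effect. No analysis plan can restore masking once scans have been read unmasked.

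**Working it through.** **1. Does any other section mask the reading?** Setting sections 4.4, 7.1.1, 7.1.2, 7.2 and 7.3 side by side, none does. Section 7.3 even creates routes by which imaging staff could learn the group. Contrast eligibility depends on being a dialysis patient or on renal function, and the nephrologist gives the radiologist written information about beta-blockade.

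**2. The plan's own figure.** Section 4.4 gives mean 2370, SD 352, a 15% difference, 1.96 and 1.28 as normal quantiles, and 22 patients per group.
- Difference: 0.15 × 2370 = 355.5.
- Formula as printed, with SD 352: 2 × (1.96 + 1.28)² × 352 / 355.5 = 20.8, so 21.
- Standard two-mean formula: 2 × (3.24 × 352 / 355.5)² = 20.6, so 21.

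Both are close to the stated 22. (The formula legend prints S as 3.52, which would give 0.21; 352 is clearly meant.) Masked reading changes none of this.

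**3. What a differential reading shift would do (illustration).** Suppose there is no true difference between two groups, but reading shifts one group's mean by b × 2370 relative to the other. For a two-sided 5% two-sample t test with n = 22 per group:
- standard error = SD × √(2/22);
- noncentrality = b × 2370 / standard error;
- degrees of freedom 42, critical value 2.018.

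Example with b = 5% and SD 352: shift 118.5, standard error 106.1, noncentrality 1.117, rejection rate 0.194.

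The shift b is assumed throughout. The SD of the change score is not in the documents; 352 is the SD of the score itself. The range therefore takes 352, twice that value (704), half the mean (1185) and the mean (2370), all as assumptions.

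| SD (assumed for change) | b = 2.5% | b = 5% | b = 7.5% |
|---|---|---|---|
| 352 | 0.085 | 0.194 | 0.373 |
| 704 | 0.059 | 0.085 | 0.130 |
| 1185 | 0.053 | 0.062 | 0.077 |
| 2370 | 0.051 | 0.053 | 0.057 |

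A larger sample makes a given shift easier to mistake for an effect: with 40 per group, b = 5% and SD 352, the rejection rate is 0.318.

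**The case against.** **The natural reading of 7.2.** The section may mean only that treatment is neither allocated nor blinded, and image-reading rules may sit in a reading manual that is not shown. This stands in part: the protocol does not say that scans will be read unmasked. But 7.2 covers blinding by name and neither defers it nor makes an exception. Masking of readers is study conduct that belongs under that heading.

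**The 10% figure.** A reader might infer from section 4.4 that up to 10% of reader bias is conceded, and that shifts of 2.5% to 7.5% are plausible because they lie below it. The documents do not support this. The figure describes repeatability between independent measurements. It says nothing about a systematic shift that differs by group, and it does not separate scanner variation from reader judgement.

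**The size of the inflation.** A reader might also quote 8%, 19% and 37% as the false-positive rates to be expected. They hold only for SD 352 on the raw scale. Section 4.4 plans regression after transformation, section 9.1 calls the score skewed and names multinomial regression, and section 9.2 corrects for the initial score. A raw-scale t test is not the planned analysis, and larger SDs bring the inflation close to nothing. This objection stands, so the table is an illustration and not an estimate.

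**Susceptibility.** The score is a quantitative CT measure. If scoring is largely automated, reader expectation matters little. The documents do not say how it is scored.

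**Relative weight.** Patient-chosen modality and dropout are separate threats that masking does not touch. That is true, but it is no reason to leave an avoidable further source of bias in an unrandomised comparison.

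**Conclusion.** The point holds as a gap in bias control that can be closed cheaply: the protocol permits unmasked reading of its primary endpoint, and masked reading is feasible. It does not establish that bias is present, nor that masking would remove all of it.

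The size is unknown. Under an assumed 5% differential shift and 22 per group, a nominal 5% pairwise test rejects between about 5% (SD 2370) and about 19% (SD 352) of the time. That range rests on an assumed shift, an assumed SD of change and a simplified test. The conclusion that reading should be masked depends on none of these numbers.

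**What to change.** In section 7.2, limit the statement of non-applicability to randomisation, treatment allocation and masking of patients and treating staff. Then add, there or under CT scanning in section 7.3, wording such as: calcium-score and coronary CT scans are coded before reading and are read by the existing reader or readers masked to treatment group and clinical data, with scan dates and the order of each patient's scans hidden.

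The cost is the logistic effort of coding and reordering images. The documents give no cost figure, but conduct of the research at one centre makes a small one plausible. No extra scans, visits or patients are needed, and the sample size is unchanged. Masking may be incomplete where an image itself gives clues to the modality. It reduces reader-expectation bias only; confounding by patient-chosen modality and selective dropout still have to be handled elsewhere.

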### **7.3 Study procedures**

*The following procedures are no part of medical treatment, thus are extra for this study:*

#### Multislice CT-scanning

Scanning with multi-slice CT is extremely fast. A calcium score scan and a coronary CT scan require less than 10 seconds of time (3 heartbeats). The scans will be performed on a MSCT-scanner with at least 64 detector rows (Brilliance-64, Philips Medical Systems, Best,

The Netherlands). In contrast to contrast-enhanced-CT scans of the heart with a considerable radiation dose, a calcium score multi-slice CT scan allows for a lower image quality and therefore a much lower radiation dose (depending on patient size and gender, radiation exposure will vary between 0.4 and 1.2 mSv, corresponding with less than half a year of natural background radiation). Even when the calcium score scan is combined with a coronary multislice CT-scan, total radiation dose is about 4-5 mSv, which is much less than the radiation dose of a diagnostic CT-scan of the abdomen (10-15 mSv). In some patients a very low dose of beta-blocker (5 mg metoprolol) will be given intravenously when the heart rate is above 60/min, in order to improve imaging of the heart during scanning. This will only be done in patients without contra-indications against beta blockade, which information has to be given to the radiologist by the nephrologist through written confirmation.

To enable assessment of coronary stenosis, the scan will be performed during contrast material injection (40-50 ml of low-osmolar contrast agent), but only in dialysis patients or in patients with adequate renal function (GFR according to MDRD formula  $\geq 45$  ml/min).

Protocol calcium score scan: prospectively triggered non-contrast CT, 128 x 0.625 mm collimation, step and shoot technique; reconstruction of 3 mm sections every 1.5 mm; 120 kVp at 50-75 mAs; radiation dose 0.8-1.2 mSv.

Protocol coronary multislice CT: prospectively triggered post-contrast CT, 128 x 0.625 collimation, step and shoot technique; reconstruction of 0.9 mm sections every 0.5 mm; 120 kVp at 150-250 mAs, depending on patient size (weight >60 kg); radiation dose 2.5-4.1 mSv; scanning during injection of 60 ml contrast material (300mg/ml iodine) at flow rate of 6 ml/s, followed by 50 ml normal saline at the same flow rate; short delay will be set to 7 s to ensure optimum contrast enhancement; scan is finished within 3 heart beats.

Risks: nephrotoxicity - but comparatively small dose of contrast material (liver exams, for example, require 150 ml; coronary require 100-300 ml, depending on difficulty of catheterization); contrast allergy - risk for serious reactions: 0.04%; contrast extravasation.

#### Pulse wave velocity

Pulse wave velocity measurements will be performed at baseline and 1, 2 and 3 years after inclusion. It can be calculated from arterial pulse contours. These are obtained by applanation tonometry (Sphygmo-Cor system, PWV Inc, Sydney, Australia) at the carotid and radial arteries and femoral artery. With this technique the artery is pressed against a hard underground (bone) with a pencil-type probe. The probe contains a strain-gauge transducer at the tip with a small pressure-sensitive ceramic sensor area (Millar Instruments, Houston, Texas, USA). To determine aortic and brachial pulse wave velocity, the distance travelled by the pulse wave over the body surface is measured as the distance between the recording sites at the femoral or radial artery to the suprasternal notch minus the distance from the recording site at the carotid artery to the suprasternal notch, as described by others. The investigation takes about 15-20 minutes.

#### Quality-of-life questionnaire

Patient's well-being will be assessed at baseline, 1, 2 and 3 years by the Kidney Disease Quality-of-Life Short Form. This questionnaire is validated for dialysis patients. Filling in the questionnaire takes about 15 minutes of time.

*The following procedures are part of standard medical treatment:*

Venipuncture at baseline and every 12 months, until 3 yr after inclusion. Venipuncture will be combined with venipuncture needed for routine care. Assessment of the routine tests (Hb, lipids, Ca, P, PTH) will be performed in the laboratory of the local treatment center. Assessment of the non-routine tests (inflammatory parameters, calcification inhibitors and serum calcification propensity) will take about 20 cc of blood per 12 month-visit, using sodium citrate and EDTA vacutainers. From February 2017 onwards, additional serum-separating vacutainers will be collected, in order to measure serum calcification propensity in active participants. A protocol concerning collection, processing and storage will be made separately under supervision of the Laboratory for Clinical Chemistry and Hematology Research, University Medical Center Utrecht.

Body weight is assessed at baseline and every 6 months, until 3 yr after inclusion. In transplant patients weight is measured at the ambulant visit. In dialysis patients, dry weight is obtained from the dialysis charts.

Blood pressure is assessed at baseline and every 6 months, until 3 yr after inclusion. In transplant patients and peritoneal dialysis patients, blood pressure is measured at the ambulant visit, in sitting position, by a sphygmomanometer. At least two readings are taken, separated by as much time as is practical; if readings vary by > 5 mmHg, additional readings are taken until two are close. In hemodialysis patients, blood pressure is taken before the hemodialysis session, again at least two readings as described above.

Medication is recorded at baseline and every 12 months, until 3 yr after inclusion: number and defined daily doses of antihypertensive drugs, number and defined daily doses of phosphate binders, number and defined daily doses of vitamin-D-analogues and calcimimetics, number and defined daily doses of immunosuppressive agents.

